## Abstract

At birth, major circulatory and pulmonary adaptations are required for a successful foetal-to-neonatal transition. In newborns with transposition of the great arteries (TGA), this transition is often impaired, leading to severe hypoxemia. This may also result in persistent pulmonary hypertension of the newborn (PPHN), worsening hypoxemia, and increasing the risk of urgent invasive interventions after birth. Physiological-based cord clamping (PBCC), delaying cord clamping until after lung aeration and ventilation are established, promotes a more stable circulatory transition and has shown benefits in both preterm and term neonates. PBCC may also provide advantages in infants with congenital heart disease. In TGA, combining PBCC with early supplemental oxygen may reduce the incidence and severity of PPHN, decrease related complications, and minimize the need for invasive interventions. To evaluate the feasibility, safety, and clinical outcomes of the stabilisation approach, we have initiated a stepwise quality improvement initiative comprising 2 sequential studies. Study phase 1, a single-centre study at Leiden University Medical Centre will assess feasibility, protocol adherence, and safety. Study phase 2, an observational cohort study across multiple European centres will evaluate clinical outcomes, focusing on incidence and severity of PPHN and the need for urgent interventions. All TGA newborns will be stabilised with an intact umbilical cord while receiving 2 L/min nasal high flow (fraction of inspired oxygen 1.0) as supplemental oxygen. Cord clamping will occur once the infant is considered stable, defined as a heart rate >100 bpm and preductal SpO_2_ >75% with supplemental oxygen. This study will inform guidelines for delivery room management and early preoperative care in TGA newborns.

At birth, major circulatory and pulmonary adaptations are required for a successful transition from foetal to neonatal circulation.^1^ Although most neonates transition seamlessly, those with congenital heart disease (CHD), such as transposition of the great arteries (TGA), often experience impaired adaptation, leading to severe hypoxemia and the need for urgent medical interventions.^2^ TGA is characterised by ventriculoarterial discordance, resulting in parallel systemic and pulmonary circulation, making postnatal arterial oxygenation dependent on foetal shunts.^3^ Effective mixing between these circulations, through an appropriately sized interatrial communication (ie, foramen ovale) or ventricular septal defect, is essential for systemic oxygenation. Increased pulmonary blood flow (PBF) and the subsequent rise in pulmonary venous return elevate left atrial pressure, promoting interatrial left-to-right shunting across the foramen ovale and enhancing oxygenation.^3^ Lung liquid clearance and aeration are the major drivers that trigger the immediate decrease in pulmonary vascular resistance (PVR) and the increase in PBF, which is then mediated by oxygen-induced pulmonary vasodilatation.^4^ The ductus arteriosus supports PBF via left-to-right shunting, increasing left atrial preload as PVR and pulmonary arterial pressure fall during neonatal adaptation.^1^^,^^4^

In neonates with TGA, particularly those with an intact ventricular septum (TGA-IVS), impaired intercirculatory mixing disrupts postnatal transition, potentially resulting in persistent pulmonary hypertension of the newborn (PPHN). PPHN further worsens hypoxemia and increases the need for invasive interventions such as mechanical ventilation and balloon atrial septostomy.^5^, ^6^, ^7^ Despite advances in prenatal detection and planned deliveries, optimising delivery room management remains challenging and underexplored in these infants. Moreover, the physiological mechanisms underlying the foetal-to-neonatal transition in TGA infants are not fully understood.^8^^,^^9^

Physiological-based cord clamping (PBCC), delaying cord clamping until after lung aeration has been established, has been shown to promote a more gradual haemodynamic transition by maintaining cardiac output, stable circulation, and oxygenation, while benefiting from optimal placental transfusion.^10^^,^^11^ Moreover, it has been shown that the vasoconstrictive response that follows immediate cord clamping (ICC) does not occur when PBCC is performed in lambs with congenital diaphragmatic hernia (CDH), and this effect also persists in the hours after birth.^12^ We therefore anticipate that PBCC, combined with early supplemental oxygen, would improve the transition in TGA neonates by reducing PVR, lowering the risk of PPHN, and minimising the need for invasive interventions, optimising early presurgical outcomes (Central Illustration). Previous studies have demonstrated that PBCC is feasible, safe, and at least as effective as standard care in preterm and term infants.^13^, ^14^, ^15^, ^16^ Moreover, a pilot randomised trial demonstrated that delayed cord clamping (DCC) in neonates with CHD, including TGA, was both feasible and safe, with a lower incidence of red blood cell transfusions compared with ICC.^17^ Given the rarity and complexity of TGA, conducting a randomised controlled trial is not feasible. Instead, we have designed a quality improvement (QI) initiative to assess the feasibility, safety, and clinical outcomes of PBCC in newborns with TGA. This approach includes PBCC with early oxygen supplementation to enhance pulmonary vasodilation and a delayed, low-dose prostaglandin regimen to limit its negative effects on respiratory drive and potential to decrease systemic vascular resistance (SVR).^8^^,^^9^ Study phase 1 comprises a single-centre feasibility and safety study at Leiden University Medical Centre (LUMC) evaluating this QI initiative. Data on protocol adherence, deviations, challenges, and safety will be used to refine the stabilisation protocol, if necessary, before its implementation across multiple European centres. Study phase 2 will evaluate the clinical outcomes of the stabilisation approach across multiple European centres.

**Central Illustration fig4:**
[figure not shown]
PBCC in newborns with TGA. FO, foramen ovale; PBCC, physiological-based cord clamping, PBF, pulmonary blood flow; RV, right ventricle; SVR, systemic vascular resistance. Created in https://BioRender.com.

## Methods

### Aim of the study

The objective of this study is to assess the feasibility, safety, and clinical outcomes of a novel stabilisation approach combining PBCC and early supplemental oxygen in newborns with TGA. The overall aim is to reduce the incidence and severity of PPHN and associated complications while minimising the need for early invasive interventions after birth. A visual summary of the study is provided in Video 1, view video online.

### Hypothesis

We hypothesise that a stabilisation approach combining PBCC with early supplemental oxygen is both feasible and safe, and will enhance transitional circulation in newborns with TGA. This approach is expected to reduce the incidence and severity of PPHN, minimise PPHN-related complications, decrease the need for urgent invasive interventions, and shorten intensive care unit (ICU) stay.

### Study design

This initiative is a prospective observational cohort study with a stepwise design (Fig. 1), progressing from problem identification and protocol development to implementation and evaluation.

**Figure 1 fig1:**

Study setup. QI, quality improvement.

#### Study phase 1 (single-centre feasibility and safety)

The initial phase will be carried out as a single-centre study at LUMC. Its primary aim is to assess the feasibility of the stabilisation protocol and identify potential safety concerns. This phase will allow for close monitoring of protocol adherence, deviations, and practical challenges, thereby allowing protocol refinements before expansion to multiple European centres.

#### Study phase 2 (multicentre clinical outcomes)

After completion of study phase 1, the study will extend into a multicentre observational cohort study across several European tertiary referral centres. The primary focus of this phase is the evaluation and description of clinical outcomes in an international cohort of neonates with TGA.

The study adheres to the SPIRIT 2022 guidelines for feasibility trials.^18^ The total patient enrolment period will span 4 years, with ongoing evaluation at each phase to inform the next steps.

### Study setting

Patient recruitment will take place at tertiary referral centres equipped with an obstetric high-care unit, a level 3 neonatal ICU, a paediatric cardiology department, and paediatric cardiac surgery facilities. After the initial feasibility and safety assessment, the study will expand to multiple European centres (Fig. 1), initially involving the following centres:•LUMC (Leiden, the Netherlands)•Semmelweis University Hospital (Budapest, Hungary)•Copenhagen University Hospital, Rigshospitalet (Copenhagen, Denmark)•Graz University Hospital (Graz, Austria)

### Study population

The study includes all prenatally diagnosed newborns with TGA (with or without ventricular septal defect) delivered at participating centres. Infants with complex TGA (ie, TGA with aortic coarctation, left ventricular outflow tract obstruction, or Taussig-Bing anomaly) are excluded.

### Study interventions

The mode of delivery will be determined based on obstetric indications and local clinical practice. TGA newborns will undergo stabilisation on purpose-built resuscitation tables, fully equipped for bedside stabilisation and resuscitation (Fig. 2). Stabilisation will adhere to local resuscitation guidelines, with the following additions as described in the study framework (Fig. 3):(1)*PBCC:* Based on the methods previously described by Knol et al.*,*^19^ umbilical cord clamping will be performed after stabilisation, defined as a stable clinical condition with adequate or optimised respiratory support and a heart rate >100 bpm. However, we will use a lower preductal oxygen saturation cutoff of at least 75% (SpO_2_ >75%), along with additional supplemental oxygen, due to the unique TGA physiology. The adjustments align with international clinical guidelines for managing TGA-IVS.^20^ The cord will be clamped between 3 and 10 minutes after birth.(2)Respiratory support: Supplemental oxygen will be initiated immediately after birth, using nasal high flow at 2 L/min with a fraction of inspired oxygen of 1.0. Early administration of supplemental oxygen aims to promote further pulmonary vasodilation, thereby reducing PVR and increasing PBF.^1^^,^^4^ The supplemental oxygen will be continued until the newborn is admitted to the (neonatal) ICU. Thereafter, it will be gradually reduced by 10% every 30 minutes, provided the clinical condition remains stable, with echocardiography performed at admission and repeated if clinically indicated, until fraction of inspired oxygen reaches 0.21. The guidelines for managing TGA-IVS recommend maintaining SpO_2_ within the target range of 75%-85%.^20^ If SpO_2_ exceeds the upper target of 85%, FiO_2_ will continue to be titrated gradually at the same rate to avoid sudden hypoxemia and pulmonary vasoconstriction.^21^ If needed, respiratory support can be increased at the discretion of the treating team, in accordance with local guidelines. Given the unique parallel circulatory physiology in TGA and the relatively low-flow oxygen therapy via high-flow nasal cannula (2 L/min), systemic hyperoxia is unlikely.(3)*Prostaglandin E2:* Prostaglandin E2 administration will be initiated approximately 3 hours after birth, following (neonatal) ICU admission and echocardiographic evaluation. The initial dosage will be approximately 0.0125 mcg/kg/min (range, 0.010-0.015 mcg/kg/min), chosen to minimise side effects, such as decreased SVR and suppression of spontaneous breathing during the transitional phase. If echocardiography identifies ductal constriction during the first examination, prostaglandin administration will be initiated sooner and/or at a higher dosage.^22^

**Figure 2 fig2:**
[figure not shown]
Concord resuscitation table. Example of the delivery room setup, using the Concord resuscitation table.

**Figure 3 fig3:**
[figure not shown]
Study framework. BAS, balloon atrial septostomy; FiO_2_, fraction of inspired oxygen; HR, heart rate; iNO, inhaled nitric oxide; LUMC, Leiden University Medical Centre; PBCC, physiological-based cord clamping; PPHN, persistent pulmonary hypertension of the newborn; QI, quality improvement; SpO_2_, saturation; TGA, transposition of the great arteries.

After stabilisation of the neonate, skin-to-skin contact with the mother (for approximately 15 minutes) is encouraged to promote maternal-infant bonding, with continuous preductal saturation monitoring and additional supplemental oxygen. During ICU admission, local routine management protocols will be adhered to, with particular attention given to general preventative measures to avoid pulmonary vasoconstriction, such as preventing hypothermia. In addition, minimal handling will be implemented to further reduce stress-related pulmonary vasoconstriction and fluctuations in oxygenation.

### Study procedures

All neonatal caregivers participating in this study are trained and accredited in neonatal resuscitation at bedside, including bedside stabilisation with PBCC. Stabilisation occurs on dedicated resuscitation tables (Fig. 2) designed to support cardiorespiratory stabilisation while the cord remains intact. A standard table setup is always available as backup. If needed, the attending neonatologist or obstetrician can decide to refrain from PBCC at any time if maternal or neonatal safety is at risk, prematurely clamp the umbilical cord, and revert to local resuscitation guidelines. All indications of early clamping (<3 minutes after birth) will be documented. After stabilisation or on ICU admission, venous access is established to enable medication administration, and arterial access is established when clinically indicated or per local protocol to allow accurate monitoring of oxygenation and metabolic status.^20^

For this study, infants will be classified as having PPHN if treated with inhaled nitric oxide (iNO) for >12 hours. The decision to initiate iNO and to assess PPHN severity will be based on a combination of pre- and postductal SpO_2_ differences (>10%) and echocardiographic findings (including ductal shunt direction and flow during systole).^23^

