### Primary outcome

#### Study phase 1

Feasibility and safety of the QI-management protocol will be assessed, including the need to discontinue the primary stabilisation approach, any protocol deviations with documented reason, and the number of adverse events in the delivery room. Safety assessments are based on any unintended events directly related to the bedside stabilisation and neonatal parameters, including:•Temperature at ICU admission•Peak haemoglobin level and the presence of polycythaemia (venous haematocrit >0.65 L/L) within 24 hours of age•Highest bilirubin level recorded during ICU admission and the need for phototherapy and/or exchange transfusion for hyperbilirubinaemia within 7 days after birth or before neonatal arterial switch operation)Maternal parameters include estimated blood loss.

#### Study phase 2

The primary clinical outcomes are the incidence and severity of PPHN, assessed by pre- and postductal SpO_2_ differences, echocardiographic findings (continuous right-to-left shunting across the ductus arteriosus from the pulmonary to the systemic circulation, or a predominant right-to-left shunt throughout systole), and the frequency, timing, and escalation of invasive respiratory and circulatory interventions.

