### Secondary outcome

Secondary outcome measures for both study phase 1 and study phase 2 include:•Timing of umbilical cord clamping: Measured in minutes after birth.•Trends in vital parameters: Heart rate, pre- and postductal SpO_2_ and blood pressure measurements will be averaged per minute and analysed for the first 72 hours after birth.•Respiratory and circulatory interventions: Frequency and types of respiratory and circulatory interventions after birth, including noninvasive and invasive respiratory interventions, administration of iNO administration, balloon atrial septostomy, and extracorporeal membrane oxygenation.•Survival proportion: Preoperative survival (ie, before arterial switch operation).•**Pressure differences across the ductus arteriosus**: Ductus arteriosus pressure gradient, estimated from Doppler-derived velocities measured by echocardiography during the cardiac cycle over the first 72 hours after birth, with measurements obtained at admission and at least once every 24 hours.

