### Statistical analysis

Feasibility will be assessed by the proportion of successful stabilisation (without protocol deviations), protocol adherence, and stabilisation-related adverse events, whereas safety will be evaluated based on the occurrence and incidence of serious adverse events. Descriptive clinical outcomes in study phase 2 include the incidence and severity of PPHN; the frequency, timing, and escalation of invasive respiratory and circulatory interventions; and the occurrence of adverse events directly related to the stabilisation approach. Outcomes will be summarised using descriptive statistics and compared with existing literature. Categorical variables will be reported as frequencies and percentages, and continuous variables will be reported as means ± standard deviations or medians with interquartile ranges, depending on distribution. Within the study cohort, comparative analyses between subgroups (eg, TGA with intact ventricular septum vs TGA with ventricular septal defect and infants with vs without PPHN) will be conducted using χ^2^ or Fisher exact tests for categorical variables and independent samples *t* tests or Mann-Whitney *U* tests for continuous variables, as appropriate. Missing data will be handled appropriately and reported. A *P* value of <0.05 will be considered statistically significant. As this is an observational cohort study, no multiplicity adjustments, stopping guidelines, or formal interim analyses for early termination are planned.

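### The phase 2 primary outcome, PPHN, has two different case rules, and the rule based on more than 12 hours of iNO does not count infants whose iNO is cut short by death or ECMO

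*Protocol article*

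**What the plan says.** Study procedures gives an explicit case rule: "For this study, infants will be classified as having PPHN if treated with inhaled nitric oxide (iNO) for >12 hours". The next sentence gives the clinical findings a different role: "The decision to initiate iNO and to assess PPHN severity will be based on a combination of pre- and postductal SpO_2_ differences (>10" per cent), together with echocardiographic findings. There they serve to start iNO and to grade severity, not to classify.

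Primary outcome, Study phase 2, reads: "The primary clinical outcomes are the incidence and severity of PPHN, assessed by pre- and postductal SpO_2_ differences, echocardiographic findings". It then specifies the ductal shunt pattern and adds "the frequency, timing, and escalation of invasive respiratory and circulatory interventions". Neither iNO duration nor a 12-hour threshold appears.

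Statistical analysis reports the incidence and severity of PPHN, compares subgroups including "infants with vs without PPHN", and compares outcomes with published literature. It does not say which case rule applies.

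Death and ECMO are collected as secondary outcomes: "Preoperative survival (ie, before arterial switch operation") and "administration of iNO administration, balloon atrial septostomy, and extracorporeal membrane oxygenation". Neither is linked to PPHN status. On care after the delivery room, the text following Figure 3 says: "During ICU admission, local routine management protocols will be adhered to".

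**The concern.** PPHN incidence is the main clinical result of phase 2. If two sections give different rules for who is a case, the plan does not determine that result, and an analyst could choose a rule after seeing the data.

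The duration rule has a second weakness. To become a case, an infant must stay on iNO for more than 12 hours. Death, or a move to ECMO at which iNO ends, can prevent that. Some of the most severe early courses would then lower the reported incidence and fall into the group without PPHN. In that comparison, every PPHN infant has by construction remained alive and on iNO beyond 12 hours, so any contrast in preoperative survival or ECMO use by PPHN status would be distorted.

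**Working it through.** The plan has no figure to reproduce. The targets of 25 and 100 newborns rest on feasibility, and no expected PPHN rate is stated.

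**Step 1: the two rules applied to the same infant.**

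| Infant | Study procedures (iNO >12 h) | Primary outcome (saturation, echocardiography, interventions) |
|---|---|---|
| Meets saturation and shunt findings, iNO for more than 12 h | case | case |
| Meets findings, starts iNO, dies by 12 h | not a case | case |
| Meets findings, starts iNO, moves to ECMO with iNO ended by 12 h | not a case | case |
| Meets findings, iNO weaned by 12 h | not a case | case |

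An infant on ECMO is missed only if iNO ended by 12 hours. Study procedures says *if*, not *only if*, so the entry *not a case* is an inference. It is needed, however, because the comparison of infants with and without PPHN requires a yes or no for every infant.

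**Step 2: how far the choice of rule could move incidence.** Inputs: N = 100 (Sample size section). Assumptions, for scale only: x infants have iNO for more than 12 h, and all of them also meet the findings; a further k infants meet the findings without more than 12 h of iNO, for any reason.

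- Incidence by the iNO rule: x/N. Incidence by the findings: (x + k)/N.
- Absolute gap: k/N. Relative gap: k/(x + k).
- Exact (Clopper-Pearson) 95% limits for y cases: the 2.5% quantile of Beta(y, N − y + 1) and the 97.5% quantile of Beta(y + 1, N − y).

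| x | iNO rule (95% CI) | k = 2 | k = 5 | k = 10 |
|---|---|---|---|---|
| 10 | 10% (4.9–17.6) | 12% | 15% | 20% |
| 20 | 20% (12.7–29.2) | 22% | 25% | 30% |
| 30 | 30% (21.2–40.0) | 32% | 35% | 40% |

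The absolute gap is 2/100 to 10/100, that is 2 to 10 percentage points. The relative gap runs from 2/32 = 6% to 10/20 = 50%.

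**Step 3: the early death and ECMO subset alone.** Each such infant moves incidence by 1/100 = 1 percentage point. The effect on the subgroup comparison can be larger. Assume x = 20 and a single preoperative death, in an infant who started iNO for PPHN and died by 12 h. As written, deaths are 0/20 with PPHN and 1/80 = 1.3% without. With that infant counted as a case, they are 1/21 = 4.8% and 0/79. One infant reverses the direction of the contrast.

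**The case against.** The best defence is that Study procedures contains the study's one explicit case rule, and Primary outcome merely lists the assessments behind incidence and severity together. On that reading the rules are nearly nested, since the saturation and echocardiographic findings are also the criteria for starting iNO. This is plausible as intent, but Primary outcome attaches its criteria to incidence as well as severity, so the text does not carry the split.

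Other parts of the defence stand and limit the point:

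- A reader might infer that the iNO rule produces a spurious reduction in favour of the hypothesis. The documents do not show this. There is no concurrent control, and the direction of any bias against the literature depends on how those sources define PPHN. The gap in the working is between two definitions in one cohort.
- A reader might count every infant who leaves iNO by 12 hours among the worst. Those weaned early may be the mildest, and a duration threshold may exclude them on purpose. Only death and ECMO are clearly problematic, and their number may be close to zero.
- A reader might attribute case status wholly to local iNO habits. Study procedures sets common criteria for starting iNO. It sets none for duration, so only that part can vary with local practice.
- Severe infants are not hidden: survival and ECMO are reported separately, and Statistical analysis already lists interventions apart from PPHN.
- With x = 20, shifts of 2 or 5 infants stay inside the 95% interval of 12.7–29.2%. That limits their practical weight but does not settle which number is the primary result.

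It can also be said that a condensed article leaves such detail to the full protocol. That could excuse silence on early death or ECMO taken alone. It does not excuse two stated rules that differ.

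**Conclusion.** The point holds in a limited form. Two sections define PPHN differently, so the phase 2 incidence and the comparison by PPHN status are not fixed by the plan. Followed as written, the rule of more than 12 hours of iNO also leaves out infants whose iNO was ended by 12 hours through death or a move to ECMO.

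The size is unknown. The range of 2 to 10 percentage points rests on assumed counts and pools all discordant infants, including those weaned early. The death and ECMO subset contributes 1 point per infant and may be small. No bias in a particular direction against the literature is established.

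**What to change.** 1. State one case definition for PPHN incidence and use it in both Study procedures and Primary outcome. Say explicitly whether the saturation and echocardiographic findings belong to incidence or to severity.
2. If more than 12 hours of iNO is kept as the case rule, also count as a case any infant who started iNO for PPHN and died or went to ECMO before 12 hours.
3. As a sensitivity analysis, report incidence by the combination of saturation difference and echocardiographic findings, regardless of iNO duration. The combination is preferable to either finding alone: Study procedures itself requires a combination, and an early right-to-left shunt may be transitional. For the same reason, making the findings the primary rule is a trade-off for the sponsor to weigh rather than a clear improvement.
4. In Primary outcome, list interventions as an outcome separate from PPHN, as Statistical analysis already does.
5. Name the chosen rule in Statistical analysis for the comparison of infants with and without PPHN.

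The cost is wording and a little extra analysis. Saturation, echocardiography, iNO, ECMO and preoperative survival are already among the planned measurements. Reported incidence may be slightly higher. Nothing here bears on when iNO is given or stopped; it settles only how outcomes are classified, and should be done before phase 2 data are analysed.
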